Gemtuzumab ozogamicin (GO) is a humanized immunoglobulin G4 antibody (hP67.6) directed against CD33 and conjugated to the DNA toxin calicheamicin via a hydrolyzable linker. GO/CD33 complexes are internalized into lysosomes, releasing calicheamicin and promoting single and double-strand breaks hereby inducing cellular death [10]. GO initially received accelerated FDA approval in 2000 for the treatment of patients aged ≥60 years with CD33 positive AML in first relapse [10]. Thereafter, a phase 3 study (S0106) was conducted by the Southwest Oncology Group (SWOG) in untreated de novo AML patients, comparing daunorubicin/cytarabine (DA) with 45 mg/m^2^ daunorubicin plus GO 6 mg/m^2^ on day 4 versus DA alone with 60 mg/m^2^ daunorubicin. The GO arm showed higher induction mortality (5.5% vs. 1.4%), without improving CR or relapse-free survival [11]. Based on these negative results, GO was withdrawn from the market in 2010. Meanwhile, results from five additional randomized studies with GO as adjunct to intensive induction therapy are available: Groupe Ouest Est d’Etude des Leuce´ mies aigue¨s et Autres Maladies du Sang (GOELAMS) AML2006IR [12], Medical Research Council (MRC) AML15 [13] and ALFA-0701 [14, 15], National Cancer Research Institute (NCRI) AML16 [16], and German-Austrian Acute Myeloid Leukemia Study Group (AMLSG) 09-09 [17]. ALFA-0701 randomized 278 patients aged 50 to 70 years with untreated de novo AML to either DA (60 mg/m^2^ daunorubicin) alone or to the same in combination with a fractionated GO induction schedule (3 mg/m^2^ on days 1, 4, and 7) [14]. Although CR with or without platelet recovery and early deaths were similar, patients in the GO arm had significantly improved median event-free (19.6 vs. 11.9 months; *P*=0.00018) and overall survival (OS) (34 vs. 19.2 months; *P*=0.046). A subgroup analysis revealed that the clinical benefit is mainly restricted to patients with favorable and intermediate-risk karyotype [14]. A meta-analysis of 3.325 patients (aged 18–84) from 5 randomized studies investigating GO as adjunct to induction chemotherapy in untreated AML concluded that the addition of GO improved OS in patients without adverse cytogenetics [18]. Rates of sinusoidal obstruction syndrome (SOS), a side effect associated with GO treatment, and 30- and 60-day mortality were lower with 3 mg/m^2^ vs. 6 mg/m^2^ GO [19]. Out of the five studies included in the meta-analysis, Castaigne et al. was the only one reporting on fractionated GO in a dosage of 3 mg/m^2^ on days 1, 4, and 7 (GO-147) [14, 18]. Interestingly, the addition of GO to induction therapy did not lead to an improved CR rate but a significantly higher rate of patients being negative for measurable residual disease (MRD-negative, 7% versus 39% in the standard and experimental arm, respectively) [20]. In addition, treatment with fractionated GO-147 was associated with a significant survival benefit in the large meta-analysis in comparison to patients that did not receive GO (OR:0.24, 99% CI 0.07–0.85), while this difference could not be shown for treatment with single-dose GO-1 (3 mg/m^2^) (OR: 1.0, 99% CI 0.78–1.3). Importantly, non-relapse mortality was not increased in patients treated with GO [14]. A major concern for patients receiving GO is the risk of SOS, especially among patients who received allogeneic hematopoietic cell transplantation (allo-HCT) within the preceding three months [21]. Revised dosing schedules significantly lowered rates of SOS to expected levels in patients being GO-naive [14, 22, 23]. Thus, the randomized comparison of GO-147 versus GO-1 as adjunct to intensive induction therapy appears as a logical consequence in terms of safety and efficacy [24].

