## Methods

### Design

The GnG study is a randomized phase III trial with MRD after induction therapy and event-free survival (EFS) as primary endpoints. The two research questions are addressed in a 2 by 2 factorial design. Patients are upfront randomized to one of the two induction schedules (GO-147 versus GO-1) and to glasdegib or placebo (double blinded) added to consolidation therapy and as single agent for 6 months’ maintenance therapy in a 1:1 ratio. The trial is designed to gain evidence of the anti-leukemic activity of GO and glasdegib in older patients with newly diagnosed AML.

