### Study setting and randomization

In Germany, patients with newly diagnosed AML are usually referred to academic Hospitals. In this study, patients will be recruited in 25 academic centers registered in the Study Alliance Leukemia (SAL) group. Participating centers are contacted by study monitors and the medical coordinator monthly to promote patient recruitment. Furthermore, after protocol amendments or upon relevant updates during the study, a newsletter will be sent to all participating centers. Conferences with the participating centers of the SAL network are done regularly to share information regarding therapy responses and complications seen within the study. Expecting at least 5 eligible patients per year and center, approximately 2 years are required to recruit the intended number of patients.

Each patient having signed informed consent and meeting all inclusion criteria is registered in the electronic case report form (eCRF). Via eCRF a unique patient ID (PAT-ID) is assigned. Following registration, eligible patients are upfront randomized 1:1 to induction chemotherapy containing either fractionated GO treatment (GO-147) or one single dose of GO (GO-1) and again 1:1 either to glasdegib or placebo (double-blinded) as adjunct to consolidation therapy and as single-agent for 6-months of maintenance therapy. Following these randomizations, 63 patients shall be allocated to each arm. Randomization is stratified by assumingly important prognostic factors age (≤70 years vs. > 70 years) and Eastern Cooperative Oncology Group (ECOG) performance status (PS) (ECOG PS = 0 vs. ECOG PS > 0). Block randomization with varying block lengths is used and performed using the web tool www.randomizer.at, by which randomization for double-blind clinical trials can easily be handled. Patients withdrawn from the trial retain their identification codes. Patients have to provide written informed consent before any protocol-specific procedures are performed. Applicable regulatory requirements, Good Clinical Practice, and ethical principles from the Declaration of Helsinki are adhered to during the study.

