### Sample size calculation and statistics

Addressing two primary endpoints, MRD-negativity after induction therapy and EFS, 252 evaluable patients are needed to reject each of the two null hypotheses at a two-sided significance level of 2.5% with a power of at least 85%.

The first primary endpoint evaluation involves the comparison of rates of MRD-negativity assessed by flow-cytometry after induction therapy between GO-147 and GO-1. Assuming a rate of MRD-negativity of 45% for GO-147 and 20% for GO-1, as well as a 3% dropout rate, a total number of 252 evaluable patients are needed to reject the null hypothesis of no difference regarding the MRD-negativity rate for patients receiving GO-147 as compared to patients receiving GO-1 during induction therapy at a two-sided significance level of 2.5% with a power of at least 85% using a chi-squared test.

The second primary endpoint evaluation involves a two-group comparison of EFS between the experimental arm of glasdegib as well as the control arm of placebo both as adjunct to standard consolidation therapy. Assuming a 2-year EFS of 38.5% for the experimental arm and a 2-year EFS of 21% for the control arm (resulting in a hazard ratio of HR=0.612), as well as an exponentially distributed dropout rate of 5% at 2 years, a total number of 224 evaluable patients (based on a number of *d*=178 required events) are needed to reject the null hypothesis assuming no difference regarding EFS for patients receiving glasdegib as compared to patients receiving placebo at a two-sided significance level of 2.5% with a power of at least 85% using a log-rank test, assuming an accrual time of 24 months, as well as a follow-up time of 24 months. This leads to a total sample size of N=max(252, 224)=252 patients to be enrolled for the whole trial to ensure a power of at least 85% for both primary endpoints.

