The MRD-negativity after induction therapy is analyzed using a generalized linear mixed model and EFS with a Cox regression frailty model. Both models are adjusted for the following fixed factors: treatment (MRD-negativity: GO-1 vs. GO-147 and EFS: glasdegib vs. placebo), age, sex, and ECOG PS, as well as for the random factor “recruiting center”. The primary analysis is based on the full analysis set including all randomized patients. Adjustment for multiple testing is done using the Bonferroni-Holm procedure in order to control the family-wise error rate at a two-sided significance level of 5% in the strong sense. Missing values for the short-term primary endpoint MRD-negativity are replaced using multiple imputation by using the fully conditional specification method [39]. Odds and hazard ratios are reported alongside with two-sided 97.5% and 95% confidence intervals, and a possible center effect is assessed by calculating the intra-class correlation coefficient and by presenting the results stratified for the center. A sensitivity analysis of the long-term primary endpoint additionally includes the interaction between maintenance therapy and induction therapy. Statistical analysis is performed using SAS v9.4 or higher.

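### The primary EFS model omits the randomised GO schedule, the other factor of the 2 by 2 design; the analysis stays valid, but adding the term would recover a little power at no cost

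*Protocol article*

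**What the plan says.** All places are in the Protocol article.

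- **Design:** "The two research questions are addressed in a 2 by 2 factorial design". Both factors are randomised upfront, each 1:1. Under Study setting and randomization: "Following these randomizations, 63 patients shall be allocated to each arm". With 252 patients this means four cells of 63, so each GO schedule makes up half of each glasdegib arm.
- **Sample size calculation and statistics, primary models:** the EFS analysis is described as "EFS with a Cox regression frailty model", and the fixed factors of the two models as "treatment (MRD-negativity: GO-1 vs. GO-147 and EFS: glasdegib vs. placebo), age, sex, and ECOG PS". Recruiting centre is the random factor. The parenthesis gives each endpoint one treatment term, and the GO schedule belongs to the MRD model only.
- **Same section, sensitivity analysis:** "A sensitivity analysis of the long-term primary endpoint additionally includes the interaction between maintenance therapy and induction therapy". This is the only place where induction therapy enters an EFS model.
- **Same section, design effect:** "a 2-year EFS of 21% for the control arm (resulting in a hazard ratio of HR=0.612", tested "at a two-sided significance level of 2.5% with a power of at least 85% using a log-rank test".
- **Discussion:** EFS was chosen partly because it reflects what induction, consolidation and maintenance each contribute. Relapse hazard ratios of 0.55 (GO on days 1, 4 and 7) and 0.82 (GO on day 1) are cited, each from comparisons with no GO.

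**The concern.** A factorial trial is normally analysed at the margins with the other randomised factor in the model. That factor is a treatment the trial itself tests, it is recorded for every patient, and here it acts early enough to matter: under Efficacy, EFS runs from randomisation and its first event type is failure to reach CR or CRi after induction.

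The Cox hazard ratio is non-collapsible. If a balanced prognostic factor is left out, the estimated hazard ratio is an average over that factor and lies closer to 1 than the ratio conditional on it, and the test loses some power. At stake is a small part of the power of the glasdegib comparison.

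There is a related point of clarity. The sensitivity analysis is described as the primary model plus an interaction. As listed, the primary model has no GO main effect. The article should say that one is fitted, because an interaction term without it can take up a GO effect and look like effect modification.

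**Working it through.** **1. Reproduce the plan's EFS figures.** Inputs from Sample size calculation and statistics: 2-year EFS 38.5% and 21%, two-sided 2.5%, power 85%, accrual 24 months, follow-up 24 months, dropout 5% at 2 years.

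- HR = ln(0.385)/ln(0.21) = 0.6116, as stated (0.612).
- Schoenfeld events: d = 4(z₀.₉₈₇₅ + z₀.₈₅)²/(ln HR)² = 4(2.241 + 1.036)²/(0.4917)² = 177.8, so 178, as stated.
- Event probability with exponential EFS, uniform accrual and exponential dropout: 0.872 (placebo) and 0.730 (glasdegib), mean 0.801. N = 178/0.801 = 222, against 224 stated, which is close enough.
- At N = 252 the expected events are 252 × 0.801 = 202.

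The design HR comes from arm-level EFS rates and a log-rank test, so it is averaged over the GO schedule.

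**2. Effect on EFS of GO-147 versus GO-1 (assumption).** The article gives none. The ratio of the cited relapse hazard ratios is 0.55/0.82 = 0.67, an indirect figure for a different endpoint. I take 0.67 as the middle case and 0.82 to 0.55 as the range.

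**3. Limit of the glasdegib HR when GO is omitted.** Let θ = 0.612 be the glasdegib HR within a GO schedule, φ the GO hazard ratio, and λ the baseline hazard, set so that placebo 2-year EFS averaged over GO is 21%. With a = 0 for placebo and 1 for glasdegib, survival averaged over GO is S_a(t) = ½[exp(−λθᵃt) + exp(−λθᵃφt)]. Solving the Cox score equation for a model with glasdegib only, under the plan's accrual, follow-up and dropout, gives the HR column below. Power is from 3,000 simulated trials per row with 252 patients, 63 per cell, tested at two-sided 2.5%.

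| Assumed GO HR on EFS | Glasdegib HR, GO omitted (GO-adjusted 0.612) | Power, GO omitted | Power, GO included |
|---|---|---|---|
| 0.82 | 0.614 | 88.4% | 88.8% |
| 0.67 | 0.620 | 87.5% | 89.4% |
| 0.55 | 0.629 | 85.6% | 88.7% |

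The shift is 0.614/0.612 to 0.629/0.612, about 0.3 to 3%. The power loss is 0.4, 1.9 and 3.1 points. The Monte Carlo standard error of each power is about √(0.88 × 0.12/3000) = 0.6 points, so the first difference is within noise.

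**4. Null case.** With no glasdegib effect, the limit is exactly 1.00 for every GO effect tried. Simulated type I error with GO omitted ran from 0.016 to 0.028 against 0.025, so it is not materially inflated.

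**5. Why the sensitivity model should be spelled out.** In the same set-up with no true interaction (2,000 trials per scenario, 0/1 coding, interaction tested at 5%), a model with glasdegib and glasdegib × GO but no GO main effect declares an interaction in 15, 46 and 81% of trials at GO hazard ratios of 0.82, 0.67 and 0.55. With the main effect in the model it does so in 5%. This shows what the wording should rule out. It is not a prediction of what the sponsor will fit.

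**Limits.** Proportional exponential hazards; no covariates or centre frailty; early induction failures not modelled separately.

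**The case against.** The strongest reply is that nothing here is wrong. GO is randomised and crossed with glasdegib, so the model without it is a valid analysis of a GO-averaged hazard ratio, which is also what the sample size targets. That stands. A reader might call the glasdegib estimate biased. The documents do not support this: there is no confounding, the shift is the gap between an averaged and a conditional hazard ratio, it vanishes under the null or if GO schedule has no effect, and otherwise it is conservative.

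A reader might also take the GO schedule to be an established source of EFS variation, since the Background reports that "patients in the GO arm had significantly improved median event-free (19.6 vs. 11.9 months". That result compares fractionated GO with no GO, whereas this trial compares GO-147 with GO-1. The Discussion leaves open which schedule is better even for MRD-negativity. The relapse ratio of 0.67 may also overstate the effect on EFS, because EFS counts induction failure and death as well, and the Background reports no gain in CR rate and similar early deaths with fractionated GO. The true effect may lie nearer 0.82, where the term makes almost no difference.

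Finally, a reader might infer that the interaction model is mis-specified. That rests on reading a condensed sentence literally. An interaction is conventionally fitted with both main effects, and nothing says that the GO main effect is left out. This objection stands as well, so only a clarification is warranted.

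What the reply does not remove is the list itself. It is explicit, it includes sex, and it omits a randomised treatment whose stage of therapy the protocol expects to contribute to EFS.

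**Conclusion.** The point holds as an efficiency improvement and a matter of consistency with the factorial design, not as an error that threatens the glasdegib conclusion. Over assumed GO hazard ratios of 0.82 to 0.55, omitting the term moves the glasdegib HR from 0.612 to between 0.614 and 0.629 and costs about 0.4 to 3 points of power. A reader might infer that the EFS comparison is underpowered; over this range it is not, since power at N=252 stays at 85.6% or more. It falls below 85% (80.5% without the term, 87.7% with it) only at a GO hazard ratio of 0.40, an extreme that nothing in the document supports. All these sizes rest on an assumed GO effect, because the article states none for EFS.

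**What to change.** Add randomised GO schedule (GO-147 versus GO-1) to the fixed factors of the primary EFS Cox frailty model, or stratify that model by it. State that the sensitivity model contains glasdegib, GO schedule and their interaction, so that the interaction term cannot absorb a GO main effect.

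The cost is one model term and one sentence. It needs no new data, patients or change of procedure, since the allocation is known for everyone. It should be fixed before the blind is broken. With the term included, the reported glasdegib HR is conditional on GO schedule, and the text should say so.

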Primary objectives of the study are (i) to assess the clinical efficacy of sequential or one-dose GO as adjunct to intensive induction therapy and (ii) to assess the clinical efficacy of glasdegib added to consolidation therapy and as a single agent for 6 months’ maintenance therapy in older patients with newly diagnosed AML.

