Secondary survival endpoints are OS (defined as time from randomization until death from any cause) and relapse-free survival (RFS) (measured from first CR/CRi to time of recurrence of the disease or death from any cause, whichever occurs first). Patients without an event are censored at the last date of follow-up. Further secondary endpoints are response (CR/CRi) after induction therapy, patient-reported outcomes (PROs) and pharmacoeconomics. PROs include assessments of a) health-related quality of life (QoL), calculated as the EORTC QLQ-C30 Summary Score [34], b) the quality of sleep or sleep disorders, calculated with the “Sleep Quality Index” from the PSQI according to the corresponding scoring guidelines [35], and c) anxiety and depression, calculated from the PHQ-4 according to the corresponding scoring manual [36]; pharmacoeconomics with health care resource utilization is assessed by self-administered resource utilization questionnaire and the SF-36 [37] [38] questionnaires for health economic analyses with patient-reported information on personal traits and experiences are collected at baseline.

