## Discussion

We designed a randomized phase-III study to compare two schedules of GO as adjunct to intensive induction therapy and to compare intensive postremission therapy with or without glasdegib (GnG-study) in a double-blinded manner. This study intends to answer two research questions: first, whether fractionated GO administered on days 1, 4, and 7 outperforms a single dose of GO on day 1 during induction therapy with the endpoint MRD status after induction therapy, and second, whether glasdegib as adjunct to consolidation therapy and as single-agent maintenance therapy for six months improves EFS.

According to the meta-analysis of Hills et al. [18], the addition of GO to induction chemotherapy significantly reduced the risk of relapse. The clinically most relevant effect was seen in the ALFA-0701 trial (risk of relapse; HR, 0.55), which administered GO on days 1, 4, and 7, compared to GO on day 1 in the MRC trials (risk of relapse; HR, 0.82). This reduction led to an improvement in survival after achieving CR and OS [18]. However, already GO-1 as adjunct to intensive induction therapy has been shown to reduce significantly the MRD level in AML with mutated *NPM1* after induction therapy [37]. Still, it is unclear which GO regimen is more effective in achieving MRD-negativity. In addition, it is of high interest whether MRD status after induction therapy can serve as a surrogate outcome for survival.

MRD-negativity assessed by real time quantitative polymerase chain reaction (RT-qPCR) in patients with AML achieving CR is known to be associated with a lower relapse risk. It can be considered a broad predictive biomarker useful to guide the patient’s postremission management [40–44]. Thus, the ELN consensus recommends molecular MRD assessments for *NPM1* mutations, *RUNX1*-*RUNX1T1*, *CBFB*-*MYH11*, and *PML*-*RARA* fusion transcripts at diagnosis, after two cycles of induction/consolidation therapy, and every 3 months, for 24 months after the end of treatment [4]. However, MRD assessment by RT-qPCR can only be applied to AML patients with suitable molecular aberrations.

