A correlation between MRD-positivity and relapse risk suggests that relapse is initiated by residual leukemia stem cells (LSC), which have shown to be resistant to conventional cytotoxic chemotherapy. In preclinical studies, glasdegib induced rapid and complete tumor regression as a single-agent or in combination with chemotherapy and reduced the expression of key leukemia stem-cell regulators hereby decreasing the leukemia stem-cell populations in patient-derived AML cells [27]. Thus, in our trial, we sought to investigate the combination of initial leukemia elimination by conventional chemotherapy and GO during the induction therapy phase and targeting of residual leukemic stem cells during consolidation and maintenance therapy with glasdegib. Efficacy of the addition of glasdegib is assessed by EFS as primary and OS as a secondary endpoint. EFS has been accepted as primary endpoint for the approval of GO in first-line therapy in AML by the FDA and EMA [47]. EFS compared to OS provides the advantage to be measurable earlier and to be directly linked to the treatment under investigation [39–50]. In contrast to overall survival, where death is the only event of interest, EFS also includes failure to obtain complete remission and relapse from complete remission. Thus, we assume that EFS as one primary endpoint will be able to better discriminate the potential contributions of the different therapeutic components (induction, consolidation, maintenance) to the overall response.

The strength of the current study is also one of its weaknesses. The 2 by 2 factorial design allows us to compare four therapy regimens. Based on known mechanisms of actions and the timely distinct use, GO in induction and glasdegib in postremission, we estimate that there will be no biometrical interaction between the investigational medical products in the trial design. Results from the meta-analysis on GO indicate that the clinical impact of GO given during induction therapy is independent of variations in consolidation therapy [18]. However, in the unlikely case of an interaction between therapies, sample size may not be sufficient to properly evaluate this interaction.

Submission to the independent Ethics Committee and the competent federal authority was completed in July 2020, and final approval was completed in November 2020. The first patient was recruited on the first of April 2021.

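### The primary EFS model leaves out the randomised GO schedule, and no GO-147 versus GO-1 EFS estimate is stated

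*Protocol article*

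**What the plan says.** The Background of the protocol article gives as the first primary objective "to assess the clinical efficacy of sequential or one-dose GO as adjunct to intensive induction therapy". The section on sample size and statistics tests this on measurable residual disease (MRD) after induction, assuming "a rate of MRD-negativity of 45% for GO-147 and 20% for GO-1". EFS is planned as a comparison of glasdegib with placebo. Each of the two hypotheses is sized "at a two-sided significance level of 2.5% with a power of at least 85" per cent, and "Adjustment for multiple testing is done using the Bonferroni-Holm procedure" across the two.

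The same section lists the fixed factors of the two models. The treatment factor is split by endpoint: "treatment (MRD-negativity: GO-1 vs. GO-147 and EFS: glasdegib vs. placebo". The other fixed factors are age, sex and ECOG performance status, with centre as a random factor. GO schedule appears in connection with EFS only once, in a sensitivity analysis that adds the interaction between induction and maintenance therapy.

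The Efficacy section names overall survival (OS), relapse-free survival (RFS) and CR/CRi after induction as secondary endpoints, without saying which randomised contrast each will serve. RFS is "relapse-free survival (RFS) (measured from first CR/CRi to time of recurrence of the disease or death from any cause", so it starts after induction.

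The Discussion states this expectation: "EFS as one primary endpoint will be able to better discriminate the potential contributions of the different therapeutic components (induction, consolidation, maintenance". It leaves the standing of MRD open: "it is of high interest whether MRD status after induction therapy can serve as a surrogate outcome for survival".

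**The concern.** The objective speaks of clinical efficacy, and the Discussion presents EFS as an endpoint that can show what induction contributes. The primary EFS model then omits the one randomised factor that concerns induction. This is a stated assignment of contrasts to endpoints, so it is more than detail left to a later document.

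At stake is how the GO result can be read. If GO-147 raises MRD-negativity, the natural next question is whether patients then live longer without failure, relapse or death. The trial observes this from randomisation in every patient, in a comparison protected by randomisation. Without a prespecified estimate, the answer is either absent or produced after the results are known. Relating MRD to relapse and survival across patients, which the Discussion also plans, is an association. It does not show that the effect of the schedule on MRD carries through to EFS.

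**Working it through.** **Inputs.** From the sample size section: 2-year EFS 38.5% and 21%; exponential dropout of 5% at 2 years; 24 months of accrual plus 24 months of follow-up; two-sided 2.5%; power 85%; N = 252. From the section on study setting and randomization: 63 patients per cell, hence 126 versus 126 by GO schedule. The documents give no hazard ratio for GO-147 versus GO-1 on EFS, so a range is assumed.

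**1. The plan's own EFS figures.**
- HR = ln 0.385 / ln 0.21 = 0.9545 / 1.5606 = 0.612.
- Events (Schoenfeld, 1:1) = 4(2.2414 + 1.0364)² / (ln 0.6116)² = 42.98 / 0.2417 = 178, as stated.
- With event hazard λ, dropout hazard η = −ln 0.95 / 24 and t = λ + η, P(event) = (λ/t) × [1 − (e^(−24t) − e^(−48t)) / (24t)]. This gives 0.872 for placebo and 0.730 for glasdegib, mean 0.801.
- Patients = 178 / 0.801 = 222, or 223 with the 179 events that the rounded HR of 0.612 requires. The plan states 224, so its figures reproduce closely.

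**2. Events available for the GO contrast.** 252 × 0.8012 = 201.9, about 202. They come from the same patients and the same follow-up.

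**3. Precision.** SE(ln HR) = 2/√202 = 0.1407. Then exp(1.96 × 0.1407) = 1.32, so the 95% CI runs from about HR/1.32 to HR × 1.32.

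**4. Power at two-sided 5%**, Φ(|ln HR| × √202/2 − 1.96), with √202/2 = 7.106:

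| Assumed HR | \|ln HR\| × 7.106 − 1.96 | Power |
|---|---|---|
| 0.67 | 2.846 − 1.96 = 0.886 | 81% |
| 0.70 | 2.535 − 1.96 = 0.575 | 72% |
| 0.75 | 2.044 − 1.96 = 0.084 | 53% |
| 0.80 | 1.586 − 1.96 = −0.374 | 35% |

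The value 0.67 is only a point of orientation. It is 0.55/0.82, the ratio of the two relapse hazard ratios quoted in the Discussion. These come from different trials, each against no GO, and concern relapse rather than EFS.

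**5. Does the interaction analysis supply the estimate?** In a model with both treatments and their product under 0/1 coding, the induction coefficient is the GO effect within the reference level of the other factor. It is not the marginal GO effect over all 252 patients, and the plan does not say that any GO hazard ratio will be reported from it.

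**The case against.** The strongest reply is that this is a condensed article. It names no contrast for any secondary endpoint, and analysing a time-to-event endpoint by the other factor of a 2 by 2 design is commonly left to the full protocol or SAP. That stands for OS and CR/CRi. Both can be compared by GO schedule as randomised, and either may be planned that way elsewhere. It carries less weight for EFS, because here the article does list the model's factors and does assign the contrast.

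A reader might infer several stronger things that the text does not support:

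- *That EFS is modelled for glasdegib only, or cannot show any induction effect.* The interaction sensitivity analysis would normally carry the induction arm. The gap concerns the primary model and a stated marginal estimate.
- *That GO will be judged on MRD alone, or its objective declared met on MRD alone.* MRD is the only primary test for GO, but no such decision rule is written. The Discussion itself narrows the first research question to MRD status.
- *That early deaths under GO-147 would go unseen.* Deaths before MRD measurement count as MRD-positive (sections on post-randomization events and on efficacy). Later deaths and relapses are not covered by this rule.
- *That RFS by GO schedule needs relabelling.* The article never assigns RFS to the GO question.
- *That the trial is powered for a GO effect on EFS.* This holds only for a strong effect. EFS also counts induction failure and death, and the Background reports similar remission rates and early deaths with fractionated GO, so an effect weaker than 0.67 is plausible.

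It is also fair to say that the sentence on EFS is Discussion prose comparing EFS with OS, and that the same section ties EFS to glasdegib. It promises no GO test on EFS. It does give a reason for using EFS that the primary model, as specified, does not serve.

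**Conclusion.** The point holds in a limited form. The primary EFS Cox frailty model omits the randomised GO schedule, and no GO-147 versus GO-1 EFS estimate is stated. This fits poorly with the GO objective and with the Discussion's reason for using EFS, and the interaction analysis is no substitute.

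The data support a useful estimate: about 202 events and a 95% CI factor of about 1.32 either way. They do not support calling it confirmatory, since power falls from about 81% at HR 0.67 to 35% at HR 0.80. The event count rests on the plan's EFS rates, dropout, accrual and follow-up. The power figures use the unadjusted Schoenfeld approximation and an assumed GO effect. Reading one GO hazard ratio across both glasdegib arms rests on the protocol's own expectation of no interaction. Whether OS and CR/CRi are compared by GO schedule cannot be settled from this article.

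**What to change.** Add GO schedule as a fixed factor in the EFS Cox frailty model, fitted in all randomised patients. Prespecify the GO-147 versus GO-1 EFS hazard ratio with its 95% CI as a secondary estimate, outside the two-hypothesis Holm family. Report it alongside the MRD result, without making the MRD conclusion depend on it. Keep the interaction model as the sensitivity analysis it already is.

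The cost is a change of wording in the protocol and SAP and one more hazard ratio from data already collected. It needs no extra patients, procedures or alpha. Because the primary EFS model gains a term, the change should be fixed before any comparison by treatment arm is seen. The small downside is that a neutral or imprecise EFS estimate would make the claim for GO more guarded.
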